**Objective:**

We aim to conduct a preliminary evaluative study comparing the sensitivity, specificity, and reliability of the BrainFx Screen (referred to as SCREEN hereafter), a novel digital tool designed to assess functional competence and detect early signs of cognitive impairment, with the Quick Mild Cognitive Impairment, a validated and highly sensitive tool that detects MCI in the older adult population. We will also investigate the perceived usefulness and integration of the SCREEN into primary care practice to identify demonstrable impacts on clinical workflow and health care providers’ (HCP) perceptions of its success as a screening tool. Patients’ perceptions of completing the SCREEN and its impact on their quality of life will also be explored.

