BrainFx is a for-profit firm that creates proprietary neurological assessment software designed to identify signs of brain function impairment. The BrainFx Screen (SCREEN) is an unvalidated, digitally administered, 15-minute, 7-question screen designed to identify early signs of MCI by assessing functional deficits that may not be readily identified by existing screens (refer to Table 1 for a summary of SCREEN activities), such as the MoCA 8.1, MMSE, and Qmci. The SCREEN is a short version of the BrainFx 360 Performance Assessment, which is designed to assess cognitive, physical, and psychosocial areas of neurofunction [74]. This is a 90-minute test administered digitally to test 26 cognitive domains across 49 tasks that are timed, scored, and subsequently compared with the Living Brain Bank (LBB), a database of all BrainFx 360 and SCREEN tests collected to date. The 7 activities used on the SCREEN were taken directly from the BrainFx 360 on the basis of clustering and regression analyses of LBB records in 2016 (N=188) [75]. The reliability of the BrainFx 360 has been validated in healthy adults (mean 22.9 years of age, SD 2.4 years), and results suggest that the overall test-retest reliability of the tool is high (intraclass correlation coefficient=0.85 [74]); however, only 2 of the 7 cognitive domains selected for the SCREEN have reliability coefficients above 0.70 (visual-spatial and problem-solving abilities). To date, BrainFx 360 has been used in clinical settings to assess neurofunction among youth and in a variety of other rehabilitation settings.

**Table 1 table1:** Summary of SCREEN activities.

Activity	Description	Time to complete (s)
Abstract reasoning	Twenty everyday items are displayed, and the patient touches the item on the screen and slides each item, one at a time, into 1 of the 5 categories into which they best belong, while being timed.	90
Constructive ability	Two rounds of a photo being displayed and breaking into 9 pieces. The patient touches the pieces and slides each piece into a grid to reassemble, while being timed.	90
Prioritizing	Five everyday activities or tasks are presented, and the patient is told what time of day it is (eg, 7 PM), and the patient touches the screen and slides each item to prioritize the order in which the activities or tasks should be completed.	60

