#### Psychometric Evaluation

Data collection for the psychometric evaluation study will take place in person at the patients’ respective FHT. Standard operating procedures have been developed for the research study, which will be followed by the research team and HCP staff trained in the study protocol and administration of all data collection tools. A member of the research team will observe at least one in-clinic HCP data collection visit to confirm adherence to the protocol and training procedures.

To assess the reliability and perceived usefulness of the SCREEN, depending upon when a patient enters the study, they may repeat the screening protocol up to 4 times. Each visit is structured around the administration of 2 MCI screens; the *GAS-10* [81,82]; and a series of questions that measure the patient’s use of technology, change in their general health and well-being, or any interactions with the health care system related to MCI that occur in the 3 months since their last appointment. The HCP will be required to complete a patient encounter form at each appointment, which includes a summary of the patient’s MCI screen results, any referrals, and their responses to these questions.

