To determine the sensitivity and specificity of the SCREEN in comparison with the Qmci, the results of both screens will be classified in binary format as healthy or not healthy, where *healthy* denotes SCREEN=no areas of challenge in all 7 activities and Qmci≥67 and *unhealthy* denotes SCREEN=1 or more areas of challenge and Qmci≤67. Consistent with consensus guidelines for screening for cognitive impairment [37,49,50], the research protocol will also require HCPs to refer patients to their primary care physician for further evaluation if they receive an abnormal score on the Qmci or significant concerns on the SCREEN. The SCREEN does not have a standardized cut-off score that can be used to classify results as abnormal. Therefore, in consultation with and on the recommendation of the SCREEN developers, for the purpose of the research protocol, a set of cut-off scores was developed to classify SCREEN results as normal (zero areas of challenge), some concerns (≤3 areas of challenge), or significant concerns (≥4 areas of challenge). All HCPs in this study will be OTs who are trained to assess individuals’ abilities or disabilities through the use of standardized testing and functional observation. As a result, the study protocol includes a condition that referral decisions for physician oversight or further testing are the purview of the HCP and their clinical judgment. This became the proxy gold standard for a positive screen in this research study.

Following the review of the results at each appointment, the HCP will provide patients with a handout that summarizes recommendations for supporting cognitive health. If the SCREEN identifies any *areas of challenge,* the patient will also receive a handout developed by BrainFx containing tailored strategies to strengthen brain health and manage deficits in those areas.

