#### Descriptive and Inferential Analysis

Descriptive data will be described using frequencies and percentiles and compared using the chi-square test or Fisher exact test as necessary. Continuous data will be analyzed for central tendency and variability; categorical data will be presented as proportions. Normality will be tested using the Shapiro-Wilk test, and nonparametric tests will be performed using the Mann-Whitney U test*.* Statistical significance will be considered at a *P* value of .05, with 90% CI provided where appropriate. We powered the exploratory analysis to validate the SCREEN using an estimated effect size of 12%, with the understanding that Canadian prevalence rates are not available [29], and determined that we needed at least 114 participants. For test-retest reliability, using 90% power and a 5% type 1 error rate, we will require a minimum of 58 test results.

MCI test outcome data will be coded into a binary format of *healthy* or *unhealthy* (where unhealthy indicates a positive result on the test, ie, 1 or more *areas of challenge* on the SCREEN results, or a score of ≤67/100 on the Qmci) to account for the difference in categorical versus continuous outcome variables. For this reason, sensitivity and specificity will be determined using cross-tabulation rather than using the area under the curve using receiver operating characteristic curves. A principal component analysis with varimax rotation will be used to better understand the derivation of components’ contribution to screen test outcomes and to explore the differences between a conventional MCI screen (Qmci) and one that is intended to be more ecologically valid by assessing functional impairment (SCREEN). Binary logistic regression will examine the effects of variables such as age, education, self-reported comfort with technology, anxiety before and after completing the MCI tests, and sleep levels on the results. The internal consistency of both the SCREEN and Qmci will be assessed using Cronbach α. Test-retest reliability, the ability of a measurement instrument to reproduce results on 2 or more occasions (ceteris paribus), will be assessed using an intraclass correlation coefficient [106].

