### Limitations

The assessment of this novel screen for MCI will be executed within the constraints of limited financial resources. As such, it will methodologically constrain our use of a presumed *gold standard* test for MCI with the participant population, which in many studies involves a neuropsychological evaluation. In fact, the presence or absence of a gold standard MCI screening test is the subject of some debate [112]. The absence of an established gold standard has resulted in the use of proxies, such as a validated, sensitive test for the same condition [107,108].

Although patient participation in the study is voluntary (there is no randomization or selection for particular traits), we anticipate that those with concerns about their cognition and those more comfortable with the use of tablet technology may be more likely to self-select into the study. Our data collection and statistical analysis will account for both the potentialities.

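### The planned SCREEN-by-Qmci table can show only agreement with the Qmci, not accuracy for MCI or any advantage over the Qmci, and the referral proxy does not repair this

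*Protocol article*

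**What the plan says.** The Abstract (Objective) describes a preliminary study "comparing the sensitivity, specificity, and reliability of the BrainFx Screen" with the Qmci. The Abstract (Methods) adds that these tests will assess the SCREEN's validity as a screening tool for MCI. The Introduction (Screening for MCI in Primary Care Settings) says the SCREEN is "designed to identify early signs of MCI by assessing functional deficits that may not be readily identified by existing screens", and names the Qmci among those screens.

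The analysis is set in two places. Psychometric Evaluation says: "To determine the sensitivity and specificity of the SCREEN in comparison with the Qmci, the results of both screens will be classified in binary format". Descriptive and Inferential Analysis codes one or more areas of challenge on the SCREEN, or a Qmci score of 67 or below, as unhealthy, and says that "sensitivity and specificity will be determined using cross-tabulation rather than using the area under the curve". No other variable is coded for this table.

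Two statements bear on the reference:
- Limitations says resources constrain the use of a presumed gold standard, and continues: "The absence of an established gold standard has resulted in the use of proxies, such as a validated, sensitive test for the same condition". That description fits the Qmci.
- Psychometric Evaluation says that referral is left to the provider's clinical judgment, and that this became the proxy gold standard for a positive screen.

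**The concern.** The Qmci is asked to play two incompatible parts. As comparator, its accuracy should be estimated alongside the SCREEN's. As reference, its accuracy is assumed perfect. Once it is the reference, the SCREEN can at best tie with it. The patients the SCREEN was built to find, those with early functional deficits that the Qmci misses, are counted as SCREEN errors.

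The Abstract (Conclusions) says the results will help the developers judge whether rigorous controlled testing is warranted. A figure labelled sensitivity or specificity for MCI would feed that decision, although it measures only how often the SCREEN repeats the Qmci's answer.

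**Working it through.** **1. What the table can identify.** The planned minimum is 114 participants (Descriptive and Inferential Analysis). Take 14 as Qmci-positive (12% of 114 is 13.7) and 100 as Qmci-negative. Suppose 10 of the 100 are positive on the SCREEN alone. Apparent specificity is (100 − 10)/100 = 90%.
- If all 10 have real early MCI, none of them is a true SCREEN error. The Qmci's own sensitivity is then 14/(14 + 10) = 58%, taking all 14 Qmci positives as true and no other cases as missed.
- If none has MCI, all 10 are SCREEN errors.

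The table is identical in both cases, so it cannot tell them apart.

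**2. Size of the distortion for an error-free SCREEN.** Let p be prevalence, and Se and Sp the Qmci's true sensitivity and specificity.
- Apparent sensitivity = p·Se / [p·Se + (1 − p)(1 − Sp)]
- Apparent specificity = (1 − p)·Sp / [(1 − p)·Sp + p(1 − Se)]

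The document gives no Qmci accuracy figures, so Se and Sp are assumptions. For p, 12% is taken from the sample-size sentence, which calls it an effect size while discussing prevalence, so its use as prevalence is also an assumption. The 42% is the upper figure in the section MCI Disorder.

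Worked case, Se = Sp = 0.80:
- p = 0.12: sensitivity 0.096/(0.096 + 0.176) = 35%; specificity 0.704/(0.704 + 0.024) = 97%.
- p = 0.42: sensitivity 0.336/(0.336 + 0.116) = 74%; specificity 0.464/(0.464 + 0.084) = 85%.

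| Assumed Qmci Se / Sp | Apparent sens / spec, p = 12% | Apparent sens / spec, p = 42% |
|---|---|---|
| 0.70 / 0.90 | 49% / 96% | 84% / 81% |
| 0.80 / 0.80 | 35% / 97% | 74% / 85% |
| 0.90 / 0.90 | 55% / 99% | 87% / 93% |
| 0.95 / 0.95 | 72% / 99% | 93% / 96% |

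The two columns have different causes. Low apparent sensitivity comes from Qmci false positives that a perfect SCREEN rightly calls negative. Reduced apparent specificity comes from MCI cases that the Qmci misses and the SCREEN finds. At 12% prevalence the first effect is much the larger.

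**3. The bias can run the other way.** If the SCREEN made exactly the same errors as a Qmci with Se = Sp = 0.80, the table would show 100% and 100%, while the SCREEN's true values would be 80% and 80%.

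**4. SCREEN-only positives will be common in any case.** An activity is an area of challenge at 1 SD or more below the reference mean (The SCREEN), and one of seven makes the result positive. For normally distributed scores that match the reference, 1 − Φ(1)^7 = 70% of people are positive if the activities are independent. Simulation gives 48% at an assumed correlation of 0.5 and 38% at 0.7. The false-positive cell will therefore hold many patients, and the table cannot say which of them have a real deficit.

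**5. Would provider referral serve as the reference?** Psychometric Evaluation has the provider review both results with the patient, and requires referral for an abnormal Qmci or for four or more SCREEN areas of challenge. Referral thus incorporates both tests, and accuracy against it would be circular. The table also counts one to three areas as positive, a range in which referral rests on judgment. The analysis section does not code referral at all.

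**The case against.** **Referral is also named as the reference.** A reader might infer that the Qmci is the sole reference throughout. The document does not support that, because it also names referral. Under that reading, a patient with a Qmci score above 67 and four or more areas of challenge would be referred and could count as a true positive. This stands as a correction to any claim of a single reference. It does not rescue the accuracy analysis, since referral depends on both tests.

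**The limitation is disclosed and the study is preliminary.** The document says no gold standard exists, that resources rule out the usual one, and that a proxy is used. No superiority hypothesis is stated, and the listed first objective is to evaluate psychometric properties. All true. Disclosure nevertheless leaves the wording of the aim and the analysis unchanged, and nowhere does it say that SCREEN-only detections will be scored as errors.

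**The size depends on assumptions.** This stands. A reader might infer that a good SCREEN must look poor, or take 35% as the expected result. Prevalence alone moves that figure to 74%, Limitations expects people with cognitive concerns to self-select, and correlated errors could inflate the result.

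**Follow-up data.** A reader might also infer that repeat visits serve only reliability. They do not: Psychometric Evaluation adds perceived usefulness, and the GAS-10 section uses change in anxiety between visits.

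**Conclusion.** The point holds for the accuracy aim. The described cross-tabulation cannot estimate the SCREEN's sensitivity or specificity for MCI, nor compare its accuracy with the Qmci's; it estimates agreement. This follows from the structure of the table and needs no assumption.

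The size is illustrative. Across the assumed Qmci values tabulated, an error-free SCREEN would show apparent sensitivity of 35–72% at 12% prevalence and 74–93% at 42%, and specificity of 96–99% and 81–96% respectively. With errors shared between the screens, the direction could reverse.

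It would go too far to say the study cannot meet its objectives. Test-retest reliability, internal consistency, the principal component analysis, and the workflow and user-perspective aims do not depend on a reference standard and are unaffected.

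**What to change.** 1. Reconcile Psychometric Evaluation, Descriptive and Inferential Analysis, and Limitations so that one reference is stated for the table. Do not treat provider referral as an independent reference.
2. Report the table as positive percent agreement (both positive ÷ Qmci-positive) and negative percent agreement (both negative ÷ Qmci-negative). In the Abstract and Methods, drop the claims of sensitivity and specificity for MCI and of accuracy compared with the Qmci. The proportions are computed exactly as planned; only their name and interpretation change.
3. Optionally, as exploratory work only, take patients with a visit-1 Qmci above 67 and compare later Qmci of 67 or below, and change in Qmci score, by visit-1 SCREEN result. State that events will be few, that follow-up is short (two to four test pairs 12 weeks apart, with collection interrupted in March 2020), and that the Qmci may have practice effects. The visit records include "any interactions with the health care system related to MCI that occur in the 3 months since their last appointment", but MCI work-up or referral should not be an outcome, because the SCREEN result can itself trigger it.

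The cost is some rewording, one optional analysis of data already collected, and a more modest headline claim. The Abstract says analysis is still in progress, so the change remains feasible. A claim of accuracy for MCI would need a reference independent of both screens, and Limitations says resources constrain the use of the usual one.

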#### The Qmci Screen

The Qmci is a sensitive and specific screen that differentiates normal cognition from MCI [63,65]. The HCP will administer the screen by asking the patient questions and recording their response on a dedicated Qmci assessment form provided by the screen developers. The patient will be required to answer 1 question via paper and pencil. The Qmci takes approximately 5 minutes to complete, is scored by hand out of 100 points, and evaluates 6 cognitive domains: orientation (10 points), registration (5 points), clock drawing (15 points), delayed recall (20 points), verbal fluency (20 points), and logical memory (30 points) [68]. The overall cut-off score to distinguish normal cognition from MCI on the Qmci is ≤67, from cognitive impairment (MCI or dementia) ≤62, and dementia alone ≤54 [88]. Although not as broadly adopted as the MoCA 8.1 in Canada, its psychometric properties, administration time, and availability for use suggest that Qmci is the optimal market assessment tool for MCI screening in FHT settings.

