The patients’ first appointment will take approximately 45-60 minutes (to account for onboarding), and all subsequent appointments (up to 4 screening test pairs, depending on the patient’s study entry date) will take approximately 45 minutes to complete. Rolling recruitment of patients will occur over an 18-month period and will end when a minimum of 2 and a maximum of 4 SCREEN-Qmci test pairs are completed every 12 weeks. In older adults, with no diagnosis of MCI or dementia, measures of cognitive abilities, including verbal fluency, attention, and intelligence [100], and measures of executive functioning [101] remain stable for anywhere from 4 to 8 weeks or from 1 to 5 years between test and retest (controlling for the effects of normal aging [100]). To date, there are no clear guidelines on the optimal time between tests [102,103]. Streiner [104] recommends longer periods to avoid recall bias. Furthermore, greater practice effects are experienced with shorter test-retest intervals [62]. The 3-month interval was therefore selected to minimize such confounds and is justified given the stability of the constructs under investigation. A randomization process will determine the order of screen administration at each visit. The Qmci will be administered using a pen and paper. HCPs will be provided with identical tablets, preloaded with the SCREEN app software.

The GAS-10 will be administered just before and immediately after the administration of the first MCI screen (eg, the SCREEN) and immediately followed by the administration of the second MCI screen (eg, the Qmci) at each appointment. After completing the 2 MCI screens, the HCP will manually calculate the results for the Qmci, log in to the BrainFx portal to retrieve the SCREEN report, and review both sets of results with the patient. The Qmci cut-off score for distinguishing MCI from normal cognition is ≤67/100 [88]. The SCREEN does not include scoring guidelines for a cut-off score but identifies whether a score on any of the 7 tasks is an *area of challenge*.

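### The classification sentence puts a Qmci score of exactly 67 in both the healthy and the unhealthy class, against the coding rule in the analysis section

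*Protocol article*

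**What the plan says.** The cut-off on the Qmci is stated in four places in the protocol article.

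- The Qmci Screen (under Measures): "The overall cut-off score to distinguish normal cognition from MCI on the Qmci is ≤67".
- Psychometric Evaluation, where the visit procedures are described: "The Qmci cut-off score for distinguishing MCI from normal cognition is ≤67/100".
- Psychometric Evaluation, in the sentence that opens "To determine the sensitivity and specificity of the SCREEN in comparison with the Qmci": healthy "denotes SCREEN=no areas of challenge in all 7 activities and Qmci≥67", and unhealthy "denotes SCREEN=1 or more areas of challenge and Qmci≤67".
- Descriptive and Inferential Analysis: a positive result, coded unhealthy, is one or more areas of challenge on the SCREEN or "a score of ≤67/100 on the Qmci". This paragraph adds that sensitivity and specificity will come from cross-tabulation and not from a receiver operating characteristic curve.

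Psychometric Evaluation also groups SCREEN results into three bands. The first two are "normal (zero areas of challenge), some concerns (≤3 areas of challenge"; the third, significant concerns, is four or more. These bands are introduced in connection with referral.

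**The concern.** A binary classification has to put each possible score in exactly one class. In the sentence that defines the classes for the accuracy analysis, 67 is in both. The analysis has no threshold-free companion that would absorb an error at the boundary, so the placing of 67 feeds directly into the two-by-two table. The Qmci is also scored by hand at the sites, so the written rule should leave nothing to interpretation.

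Two lesser points of wording lie next to it. The sentence joins the SCREEN condition and the Qmci condition with *and*, while the analysis section uses *or*. And the SCREEN bands for normal and for some concerns both admit a patient with zero areas of challenge.

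**Working it through.** **No stated figure to reproduce.** The point concerns a rule. The check is to apply each version of the rule to every whole-number Qmci score from 0 to 100.

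| Rule | Healthy | Unhealthy | Scores in both | Scores in neither |
|---|---|---|---|---|
| Psychometric Evaluation, classification sentence | ≥67 | ≤67 | 67 only | none |
| Descriptive and Inferential Analysis | complement, >67 | ≤67 | none | none |

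The overlap is one score. The statements in The Qmci Screen, in the visit procedures and in the analysis section agree with each other, and with the unhealthy half of the classification sentence. The healthy half is the only outlier.

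**How many patients could score 67.** The inputs are:

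- 114 participants, from Descriptive and Inferential Analysis.
- 12% at or below 67. The article gives 12% as the estimated effect size for the validation analysis. Using it as the share of Qmci positives is my assumption.
- Normally distributed scores with a standard deviation (SD) of 8 to 12. This is also an assumption; the article gives neither a mean nor an SD.

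For whole-number scores, 12% at or below 67 means P(X < 67.5) = 0.12, so 67.5 lies at z = −1.175. The lower edge of the score 67 is 66.5, at z = −1.175 − 1/SD. Hence

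P(score = 67) = 0.12 − Φ(−1.175 − 1/SD).

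- SD 8: 0.12 − Φ(−1.300) = 0.12 − 0.0968 = 0.0232; × 114 = 2.6 patients.
- SD 12: 0.12 − Φ(−1.258) = 0.12 − 0.1041 = 0.0159; × 114 = 1.8 patients.

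Expected positives are 0.12 × 114 = 13.7, so patients at exactly 67 would be 1.8/13.7 = 13% to 2.6/13.7 = 19% of them.

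**Dropping the 12%.** With assumed means of 67 to 76 and SD 8 to 15, the share at exactly 67 is 2.2% to 5.0%, or 2.5 to 5.7 of 114. The larger counts come with many more positives: mean 70 and SD 8 gives 5.3 patients at 67 but 43.0 at or below 67, whereas mean 76 and SD 8 gives 3.0 and 16.4. The high counts at 67 must not be set against about 14 positives.

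**Illustrative adverse case.** Suppose there are 14 Qmci positives, two of them score exactly 67, both are SCREEN-negative, and 10 of the other 12 are SCREEN-positive. Sensitivity is 10/14 = 71% with 67 coded unhealthy and 10/12 = 83% with 67 coded healthy, a difference of 12 percentage points. This needs every patient at 67 to be SCREEN-negative, so it is an extreme and not an expected shift.

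**The SCREEN bands.** Zero areas of challenge satisfies both the first band and ≤3. The cross-tabulation uses zero against one or more, so the overlap does not enter it.

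**The case against.** The strongest reply is that the analysis section already settles the matter. It names ≤67 as positive, the coding is binary, and healthy is therefore the complement. Two other statements of the cut-off agree. This reply largely stands, and it limits what may be concluded.

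- A reader might infer that the reference classification is undefined at the cut-off. The article does not support that: its majority reading is clear, and the section that governs the analysis follows it.
- A reader might infer that 67 could be assigned after the SCREEN results are known. The analysis section fixes 67 as positive in advance, so recoding it would depart from the stated plan.
- A reader might infer from *and* that discordant patients, positive on one tool only, belong to neither class and that the table loses its off-diagonal cells. But the same sentence says that the results of both screens are put in binary form, and the analysis section joins the two conditions with *or*. Each tool is evidently coded separately.
- A reader might infer a shift of 10 points or more in sensitivity as the likely effect. That needs the adverse case shown above, and the score distribution behind it is assumed.
- The overlap of the SCREEN bands is a slip in the referral grouping. Zero has its own named band, so the intention is plain enough.

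What the reply does not remove is the contradiction itself. Two sections of one article give different rules for the same score, the faulty one is the sentence that defines the accuracy comparison, and nothing says which governs. Condensing a protocol for a journal does not explain it, since both halves of the rule are printed in full.

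**Conclusion.** The point holds as a contradiction in an operative threshold. The classification sentence in Psychometric Evaluation puts 67 in both classes, and its healthy limit conflicts with the three other statements of the cut-off. The intended rule is recoverable, so this is a correction of wording with a small and bounded effect. It touches only patients who score exactly 67: about 2 to 3 of 114 if 12% score 67 or below, under normal scores with SD 8 to 12. The SD and the use of 12% as the share of positives are assumptions. The direction and size of any change in sensitivity or specificity cannot be stated from the article. The overlap of the SCREEN bands at zero is a minor wording point with no effect on the cross-tabulation.

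**What to change.** In the classification sentence of Psychometric Evaluation, for the analysis classification only, change the healthy limit from Qmci ≥67 to Qmci >67. This matches the coding in Descriptive and Inferential Analysis (unhealthy ≤67) and puts every score from 0 to 100 in exactly one class.

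In the same place, say that SCREEN (zero against one or more areas of challenge) and Qmci (>67 against ≤67) are coded as two separate binary variables, and that the two-by-two table is formed from them.

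Reconcile the SCREEN bands so that a result of zero belongs to one band only. Because these bands bear on referral, how they are reworded is for the investigators.

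The cost is a sentence or two. No new data and no change to the sample size are needed.

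### Two reference standards are named for a positive screen, the Qmci and the therapist's referral decision; the second depends partly on the SCREEN result, so only the Qmci should serve as reference

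*Protocol article*

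**What the plan says.** **The Qmci as reference.** The Psychometric Evaluation section introduces its binary coding with the words "To determine the sensitivity and specificity of the SCREEN in comparison with the Qmci". The cut-off is given there: "The Qmci cut-off score for distinguishing MCI from normal cognition is ≤67/100". Descriptive and Inferential Analysis repeats the coding, with a positive result being 1 or more areas of challenge on the SCREEN "or a score of ≤67/100 on the Qmci", and adds that "sensitivity and specificity will be determined using cross-tabulation". Limitations defends the absence of a full diagnostic work-up in terms that fit the Qmci: "The absence of an established gold standard has resulted in the use of proxies, such as a validated, sensitive test for the same condition".

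**The referral decision as reference.** The same Psychometric Evaluation section requires patients to be referred to their physician "if they receive an abnormal score on the Qmci or significant concerns on the SCREEN", where significant concerns means 4 or more of the 7 activities flagged as areas of challenge. It then places referral decisions within the therapist's clinical judgment and concludes: "This became the proxy gold standard for a positive screen in this research study".

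**What the therapist knows.** Still in that section, the therapist scores the Qmci by hand, retrieves the SCREEN report from the portal and goes through both results with the patient. Nothing describes a referral decision made without sight of the SCREEN.

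**The concern.** A diagnostic accuracy analysis needs one reference, and that reference should not depend on the index test. Here one section names two, and the second fails that condition. A patient referred because the SCREEN shows 4 or more areas is SCREEN-positive by definition and can never count as a false positive. Such patients move out of the reference-negative group into the true positives, which raises the apparent sensitivity and specificity of SCREEN whether or not it detects impairment.

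Psychometric evaluation is the first listed objective, and the Abstract says the results will help the developers judge whether rigorous controlled testing is warranted. The same data give different accuracy figures under the two references, so the article should say which one applies.

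A related question is what may be claimed. The Objective speaks of "comparing the sensitivity, specificity, and reliability of the BrainFx Screen" with the Qmci. When the Qmci is the reference, the table measures how far SCREEN agrees with it; it cannot rank the two tools on sensitivity for MCI.

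**Working it through.** The article states no accuracy figure, so there is none to reproduce. The check sets the two references side by side and works out what changes.

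**1. Direction, in general.** Take referral to be exactly the stated triggers: Qmci ≤67, or SCREEN with 4 or more areas. SCREEN is positive at 1 or more areas, as the article defines it. Let P and N be the numbers of Qmci-positive and Qmci-negative patients, a the SCREEN-positives among P, d the SCREEN-negatives among N, and c the patients among N with 4 or more areas.

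- Against the Qmci: sensitivity = a/P, specificity = d/N.
- Against referral: sensitivity = (a + c)/(P + c), specificity = d/(N − c).

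Adding c to the numerator and denominator of a fraction below 1 raises it, and so does removing c from the denominator alone. Both measures therefore rise whenever c > 0, a < P and d > 0.

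**2. Illustration.** All counts are assumed except the total of 114, which is the article's planned minimum. P = 14, N = 100, a = 10, SCREEN-positive in 50 of N (so d = 50), c = 10.

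| Reference | Sensitivity | Specificity |
|---|---|---|
| Qmci ≤67 | 10/14 = 71% | 50/100 = 50% |
| Referral triggers | (10 + 10)/(14 + 10) = 20/24 = 83% | 50/(100 − 10) = 50/90 = 56% |

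The Youden index (sensitivity + specificity − 1) goes from 0.21 to 0.39 with no change in the data. False positives remain under the referral reference: 50 − 10 = 40 Qmci-negative patients have 1 to 3 areas, so they are SCREEN-positive but not referred under the triggers.

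**3. A SCREEN that carries no information.** Suppose SCREEN is independent of the Qmci. Let q be the proportion Qmci-positive, and s1 and s4 the proportions with at least 1 and at least 4 areas. Then, against the triggers:

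- sensitivity = (q·s1 + (1 − q)·s4)/(q + (1 − q)·s4)
- specificity = (1 − s1)/(1 − s4)

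s1 and s4 were simulated from seven normal activity scores cut at 1 SD below the mean, with an assumed common correlation. At correlation 0.3, s1 = 0.561 and s4 = 0.067. With q = 0.12:

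- sensitivity = (0.067 + 0.059)/(0.120 + 0.059) = 0.71
- specificity = 0.439/0.933 = 0.47
- Youden index = 0.18

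Against the Qmci the same SCREEN gives 0.56 and 0.44, a Youden index of 0. Over q from 12% to 42%, the spurious index is 0.01 to 0.03 at correlation 0, 0.07 to 0.18 at 0.3, and 0.12 to 0.28 at 0.5. The 12% and 42% are borrowed from the article only as illustrative rates; it calls the first an effect size and quotes the second as an upper MCI prevalence.

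**4. The role of judgment.** The article also leaves referral to clinical judgment. If therapists referred on any area of challenge, specificity would be 1.00 by construction and sensitivity of an uninformative SCREEN 0.68 to 0.95 over the same assumed range. If they overrode the triggers in other ways, the size could differ either way. Judgment does not remove the dependence, because the SCREEN report has been seen.

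**The case against.** The strongest reply is that the planned analysis does not use referral. The sentence introducing sensitivity and specificity names the Qmci, the statistical section codes only SCREEN and Qmci for the cross-tabulation, and Limitations describes a validated test. On that view the gold-standard sentence is loosely worded and describes workflow. This largely stands: a reader might infer that the specified accuracy analysis is already biased, or that the sponsor means to report the more favourable figure, and the documents support neither. What remains is that the sentence calls referral the gold standard for this study and nothing withdraws it.

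A reader might also infer that specificity against referral must be 100%. That would need SCREEN-positive to mean 4 or more areas, or referral on any area. The accuracy analysis counts 1 or more, and 4 or more is only a referral category. At the protocol's cut-off the shift can be modest, as the lower end of the range in the working shows.

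It is also fair to say that the Qmci is itself an imperfect proxy and that the article partly discloses this: Limitations admits that resources rule out a neuropsychological standard, and the Objective calls the study preliminary. Any figure for the resulting distortion would rest on assumed Qmci accuracy and on the two tests erring independently, so none is offered here. Finally, the abstract does not expressly promise to estimate the Qmci's own sensitivity; that is one reading of a condensed sentence, which is why the point about comparative claims concerns wording only.

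**Conclusion.** The point holds as an unresolved conflict over the reference standard. The Psychometric Evaluation section names both the Qmci and the referral decision, the other sections point to the Qmci, and no text settles which governs. If referral were used, SCREEN would be judged partly against itself, and both accuracy measures would tend to rise: from 71% and 50% to 83% and 56% in the illustration. Those sizes depend on assumed counts and on referral following the stated triggers exactly; the direction under those triggers follows from the algebra. The Qmci cross-tabulation as written is free of this bias, so what needs correcting is the text that would allow a biased estimate.

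**What to change.** Delete or reword the gold-standard sentence in Psychometric Evaluation so that Qmci ≤67 is the only reference for the accuracy cross-tabulation. Report referral only as a descriptive workflow outcome, which suits the second objective. Describe the results as positive and negative percent agreement with the Qmci, and do not present them as the two tools' comparative sensitivity for MCI. Kappa, or a sensitivity analysis over assumed Qmci accuracy, is optional. No new scoring rule is needed, since the procedures already list scoring the Qmci before retrieving the SCREEN report.

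Separately, reconcile the statement that referral is required on fixed triggers with the statement that it rests on the therapist's clinical judgment. Which of the two applies is for the investigators to state.

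The cost is wording only, with no new data. The price is a more modest claim of validity.
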